
### Control

We will use a waiting list as the control group. In fact all registrants will be exposed to the intervention but those who register late will be kept in waiting list and as indicated with be treated as control group for the study. Thus, participants who will be assigned to this group will receive an e-mail message every 3 weeks to keep them involved in the study during the intervention period but they will not have access to the My Healthy Heart Profile and they will not know that they are control group. The e-mail messages will contain general information about metabolic syndrome and healthy nutrition and benefits of fruit and vegetable intakes, physical activity and body weight loss. However, one should notice that such a control group in essence is an intervention group and not a true control group.

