**Methods/design:**

This is a two-arm randomized controlled trial. The study includes 160 participants (n = 80 per arm) who will be recruited via online registration on the study website. The inclusion criteria are that they should have metabolic syndrome and have access to the Internet. All participants will receive information on dietary intake and physical activity through the study website. The intervention group will receive additional resources via the study website including interactive Healthy Heart Profile and calorie restricted diet tailored to the participants. The primary outcomes are feasibility, acceptability, usability, and the change in metabolic syndrome components. The secondary outcomes are comparing quality of life, physical activity and food intake among the study arms. The participants will be followed up to 6 months with data collection scheduled at baseline, 3 and 6 months.

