## Methods

### Trial design

This study is an interactive web-based randomized trial (using pre and post-intervention assessments). Participants in this parallel study randomly will be assigned to one of two conditions: the intervention group and the waiting list group (the control group). Participants will be assessed at three points in time: at baseline, three and six months follow-up. Study procedure from enrollment through follow up data collection and analysis are depicted in Figure 1.

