### Randomization

Randomization will be carried out after baseline measurements. Participants will be randomly assigned to the trial arms. Randomization sequence will created manually by a biostatistician using Excel software [Command in the Excel for random block sizes column: *=rand()*] [73] to assign participants to the study arms using a 1:1 allocation ratio with block size of 4. The allocation sequence will conceal from the investigators in sequentially numbered, opaque, sealed and stapled envelopes.

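### The Control section treats late registrants as the control group, which contradicts the concealed 1:1 random allocation in the rest of the protocol

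*Protocol article*

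**What the plan says.** Three parts of the protocol article describe random allocation. The abstract states: "This is a two-arm randomized controlled trial". Trial design states: "Participants in this parallel study randomly will be assigned to one of two conditions", and names these as the intervention group and the waiting list group, which is the control. Randomization gives the mechanism: "Participants will be randomly assigned to the trial arms", "using a 1:1 allocation ratio with block size of 4". It fixes the timing, "Randomization will be carried out after baseline measurements", and the concealment: "The allocation sequence will conceal from the investigators in sequentially numbered, opaque, sealed and stapled envelopes".

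The Control section, which defines the comparator, says that all registrants will be exposed to the intervention but that "those who register late will be kept in waiting list and as indicated with be treated as control group for the study". Its next sentence speaks of participants assigned to this group and bars them from My Healthy Heart Profile while the intervention period lasts. That period is not defined there.

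**The concern.** Under the Randomization section, the next envelope decides the arm, after baseline. Under the Control section, the date of registration decides it, before any clinic visit. A participant cannot be a control by both rules.

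If the second rule were used, three things would be lost:

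- Arm would be aligned with calendar time and with whatever distinguishes early from late registrants.
- The arm would be known before eligibility and baseline were settled, so the envelopes would conceal nothing.
- The t-tests and the mixed model in Statistical analysis would compare groups that chance did not form. No adjustment for registration time is named there. None could replace randomisation, because the two arms would share no stretch of registration time.

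This is not a detail that a condensed article leaves to a fuller document. It is a positive statement of a non-random rule.

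**Working it through.** The contradiction needs no arithmetic, and the plan has no figure of its own on this point to reproduce. The calculation below shows only what would follow if the late-registration rule were applied.

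**Inputs from the protocol.** The abstract gives the total: "The study includes 160 participants (n = 80 per arm) who will be recruited via online registration". Randomization gives 1:1 allocation in blocks of 4. Sample size gives 60 per arm before the attrition allowance and a standard deviation of 2.5 for waist circumference. Statistical analysis gives a two-sided 5% level. Whether 60 follows from its own inputs is a separate matter and does not affect this point.

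**Assumption, not in the protocol.** The outcome drifts linearly by a total of D (in SD units) from first to last registrant, with no true treatment effect. D is shown as a range.

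**Step 1: separation of the arms in registration order (ranks 1 to 160).**

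- Late registrants as controls, taken as first 80 against last 80: mean ranks are (1 + 80)/2 = 40.5 and (81 + 160)/2 = 120.5, a difference of 80. The correlation between arm and order is 0.87.
- Permuted blocks of 4, from 20,000 simulated lists: the mean rank difference averages 0.0 (SD 0.20, largest 0.78). The correlation is at most 0.008 in absolute value.

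**Step 2: bias.** The drift per rank is D/159, so the late-registrant rule biases the contrast by D × 80/159 = 0.503 D, or about D/2. Under blocks of 4 the expected bias is essentially zero.

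**Step 3: type I error.** With bias b = D/2 and SE = √(2/n) in SD units (normal approximation), type I error = 1 − Φ(1.96 − b/SE) + Φ(−1.96 − b/SE). SE is √(2/80) = 0.158 for 80 per arm and √(2/60) = 0.183 for 60 per arm.

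Example with D = 0.5 and n = 80: b/SE = 0.25/0.158 = 1.58, so type I error = 1 − Φ(0.38) + Φ(−3.54) ≈ 0.35.

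| D (SD) | Bias (SD) | Bias in waist at SD 2.5 (cm) | Type I error, 80 per arm | Type I error, 60 per arm |
|---|---|---|---|---|
| 0.1 | 0.05 | 0.125 | 6% | 6% |
| 0.25 | 0.125 | 0.3125 | 12% | 11% |
| 0.5 | 0.25 | 0.625 | 35% | 28% |
| 1.0 | 0.5 | 1.25 | 89% | 78% |

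The 60-per-arm column assumes that losses are spread evenly over registration order.

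**The case against.** The strongest reply is that the sentence is loose writing. The abstract, Trial design and Randomization all describe random allocation, and Randomization does so in operational detail. Trial design already equates the control group with the waiting list, so the back-reference inside the Control sentence may point there, and the text that follows returns to the language of assignment. No date, cut-off or count defines late, so the sentence could hardly work as an allocation rule. This stands as far as it goes: a randomised waiting list is a plausible meaning. It does not save the sentence, which still says something else and is the rule a reader meets in the section on the control group.

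Several stronger readings are tempting but not supported:

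- A reader might infer that the trial is not randomised, or that some participants have been allocated by date. Nothing in the article shows that.
- A reader might infer that the 6-month contrast is diluted because the waiting list gains early access. The Control section bars controls from the profile during the intervention period. The only gap is that this period is not expressly tied to the 6-month assessment.
- A reader might infer that a drift over recruitment passes in full into the treatment estimate. For a linear drift only about half does.
- A reader might suppose that early registrants are keener, were reached by different posters or joined in a different season. Recruitment gives no timetable or season and no data on motivation, so these are conjectures.

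**Conclusion.** The contradiction is certain: the late-registration sentence is incompatible with Trial design and Randomization, and the article does not resolve it. It must be corrected, because the claim to be a randomised trial rests on which rule applies.

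The bias is conditional. It arises only if the sentence is followed as written, and its size depends on a drift that the protocol does not give. Over the assumed range of 0.1 to 1.0 SD, type I error with 80 per arm would run from slightly above nominal (about 6%) to about 89%. If allocation follows the envelopes, bias from such drift is essentially nil and the fault is one of wording.

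**What to change.** In the Control section, delete the late-registration rule. State instead that every eligible registrant, whatever the registration date, is allocated only by the next sequentially numbered sealed envelope, and that the waiting list consists of those so allocated to control.

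As a minor clarification, state that the intervention period during which controls have no access to My Healthy Heart Profile runs to each control participant's own 6-month (T2) assessment.

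The cost is wording only, with no extra participants, visits or procedures.

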### Aim

The aim of this randomized controlled trial (RCT) is to determine the feasibility, acceptability, usability, and effectiveness of an interactive web-based lifestyle intervention focusing on dietary and physical activity for reducing metabolic syndrome indicators. It was hypothesized that developing and launching an interactive web-based educational program would be feasible, acceptable and will be used by target audiences, and that using interactive web-based educational program will produce a change in lifestyle behaviors and this consequently will lead to reduction in metabolic syndrome.

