### Intervention

Both intervention and control arms will be encouraged to engage in making healthy changes to their physical activity and nutrition behaviors in order to treat metabolic syndrome. The participants in intervention arm will be received the username and password to use the My Healthy Heart Profile and log-in to the interactive section of website. Participants in intervention arm will be encouraged to frequently log-in and visit their homepage or ask questions at any time they wish. For the security and confidentiality, the users will receive personal username and password. We will recommend the participants to keep the password safe and avoid sharing it with anyone. They will not able to change the password. If any one forgets the password a new one will be sent to his/her e-mails address.

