### Sample size

The sample size was calculated based on one standard deviation decrease (2.5) [85] in waist circumference as one of the most important components of MS [86]. As such a study with a power of 90% at 5% significance level would need 60 participants in each arm. Giving that there might be an attrition risk, 80 participants per each group were sought.

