### Attrition prevention

In order to prevent attrition and encourage people to take part in the study we will use five strategies appropriate to participants. Firstly, free blood testing will be carried out for all participants at all three assessment times. Secondly, the test results will send through e-mail within 24 hours. We will request from users to log-in the personal profile and record the new values. Thirdly, e-mail reminders will send to users when they are inactive for 2 weeks. Fourthly, in order to keep up to date and enhance the website visiting, the new information will be placed on the site monthly. Finally, all recruitment processes will be online.

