### Statistical analysis

The characteristics of participants will be summarize as proportions or means with standard deviations. To test the study hypotheses t-tests for independent samples will be performed. Comparisons of proportions will be carried out using the Pearson’s chi-square test without continuity correction. For all parameters 95% confidence intervals will be defined. Two-sided p values of less than 0.05 will be regarded as statistical significant. All analyses will be performed with the SPSS software version 18. Between group differences will be evaluated by intent-to-treat analysis using the Generalized Linear Mixed Models (GLMM).

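### The waiting-list control receives lifestyle education, so the trial tests only an added effect, yet the hypothesis names no comparator and the sample size rests on an undefined 2.5 decrease in waist that does not give 90% power with 60 per arm

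*Protocol article*

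**What the plan says.** Under Trial design the two conditions are "the intervention group and the waiting list group (the control group"), and the Control section repeats the waiting-list label. Other parts of the article describe what controls receive:

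- **Intervention section:** "Both intervention and control arms will be encouraged to engage in making healthy changes to their physical activity and nutrition behaviors".
- **Control section:** an e-mail every 3 weeks with general material on metabolic syndrome, nutrition, activity and weight loss. Controls have no access to the interactive profile. The section ends with the remark that "one should notice that such a control group in essence is an intervention group and not a true control group".
- **Abstract, Methods/design:** everyone gets dietary and activity information through the website, and the intervention arm gets the profile and the tailored diet on top.
- **Attrition prevention:** "free blood testing will be carried out for all participants at all three assessment times", followed by a sentence, naming no arm, that results are e-mailed.

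The Aim hypothesises that "using interactive web-based educational program will produce a change in lifestyle behaviors and this consequently will lead to reduction in metabolic syndrome". It does not say compared with what.

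On size: "The sample size was calculated based on one standard deviation decrease (2.5) [85] in waist circumference", and "a study with a power of 90% at 5% significance level would need 60 participants in each arm". The target is then raised to 80 per arm for attrition. The Statistical analysis section plans independent-samples t-tests and an intention-to-treat mixed model for between-group differences, and adds: "Two-sided p values of less than 0.05 will be regarded as statistical significant".

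**The concern.** A waiting-list label and a hypothesis with no comparator both suggest that the trial will measure the programme against nothing. It will not. Both arms are pushed in the same direction, and the between-arm contrast isolates only the interactive profile and the tailored diet. If both arms improve, a non-significant difference would mean that no benefit beyond general education was demonstrated. It would not mean that the programme fails to reduce metabolic syndrome, but the hypothesis as worded invites that reading.

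The same gap runs into the sample size. A decrease in waist circumference can be a change within one arm or a difference between arms. With an active control these can be far apart, and only the between-arm difference determines the power of the planned test. The article does not say which one 2.5 is, so the 90% cannot be tied to the comparison that will be made.

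**Working it through.** **Inputs.** Difference 2.5, SD 2.5 (one SD), 5% significance, 90% power, 60 per arm before and 80 after attrition: Sample size section. Two-sided testing: Statistical analysis section. Allocation 1:1: Randomization section. No unit is printed beside 2.5; waist is measured in centimetres under Primary outcomes. No control-arm change is given anywhere.

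**Step 1: try to reproduce 60 per arm.** For two means, n per arm = 2(z₀.₉₇₅ + z₀.₉₀)² (SD/difference)².
With the stated inputs: 2 × (1.960 + 1.282)² × (2.5/2.5)² = 21.01, so 22 per arm. The t-based solution is 22.02, so 23. The stated 60 is not reproduced.

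Other standard readings (normal formula) do not give 60 either:

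| Reading | n |
|---|---|
| One-sided 5% | 18 per arm |
| Change score with SD 2.5√2 | 43 per arm (one-sided 35) |
| Bonferroni over 6 components | 31 per arm |
| Bonferroni over 10 tests | 34 per arm |
| One-sample change | 11 |

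The attrition step is consistent with an unstated 25% loss: 60/0.75 = 80.

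**Step 2: what 60 per arm delivers.** Two-sample t-test, two-sided 5%:

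- For a difference of one SD, power is 99.97%.
- For 90% power, the standardised difference is 0.597. With SD 2.5 that is 0.597 × 2.5 = 1.49. With 80 analysed per arm it is 0.516 × 2.5 = 1.29.
- Conversely, if the difference is 2.5, 60 per arm fits 90% power only when SD = 2.5/0.597 = 4.19 (4.22 by the normal formula).

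**Step 3: sensitivity to an active control.** Let f be the share of the 2.5 decrease that controls also achieve, if 2.5 is the change in the intervention arm. The between-arm difference is then 2.5(1 − f). The values of f are assumptions, since the protocol gives none.

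| f | Difference | SD 2.5: power at 60 / 80 per arm | SD 4.19: power at 60 / 80 per arm |
|---|---|---|---|
| 0 | 2.5 | 99.97% / >99.9% | 90% / 96% |
| 25% | 1.875 | 98% / >99% | 68% / 80% |
| 40% | 1.5 | 90.3% / 96.5% | 49% / 61% |
| 50% | 1.25 | 77.5% / 88.2% | 37% / 47% |
| 60% | 1.0 | 58.4% / 71.0% | 25% / 32% |

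With SD 2.5, power at 60 per arm stays at or above 90% until controls achieve 1 − 0.597 = 40% of the 2.5; at 80 per arm, 1 − 0.516 = 48%. With SD about 4.2, any control-arm improvement takes 60 per arm below 90%.

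**The case against.** The article is more open than its label suggests. The abstract already presents the contrast as information for all plus additional resources for one arm, and the Control section volunteers the limitation. Waiting list is also not simply the wrong term: the Control section says all registrants will eventually be exposed to the intervention, so delayed access is a real feature and can coexist with general education in the meantime. Both points stand, and they are why the comparator should be described more fully rather than have its label removed.

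Three stronger readings are tempting and should not be drawn:

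- **That the trial was sized against an untreated control.** The Sample size section names no comparator and states no assumption of zero control-arm change. The 2.5 could already be net of that change. The fault is that the target is undefined.
- **That the trial is underpowered.** On the literal inputs 60 per arm is more than enough, and it tolerates controls achieving about 40% of the decrease. A shortfall needs a larger control-arm change or a larger SD, and the article settles neither.
- **That controls certainly receive the programme's feedback.** Blood testing covers all participants, but the sentence on e-mailing results names no arm, and the next asks users to record values in a profile that controls do not have. E-mailed laboratory values are in any case not shown to equal the profile's automatic messages and graphs.

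It can also be said that the wording of conclusions is usually left to the analysis plan or the report. That is fair, so no separate conclusion rule is asked for here. The hypothesis, however, is stated in this article and lacks its comparator. The failure of 60 to follow from the stated inputs does not depend on how active the controls are, and it stands regardless.

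**Conclusion.** The point holds as a fault of definition. The randomised comparison estimates the added effect of the interactive profile and tailored diet over general education and encouragement, while the hypothesis names no comparator and the sample-size target is not identified as a between-arm difference.

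As a between-arm statement, 90% power with 60 per arm for one SD is wrong: the requirement is 22 to 23 per arm, and the power at 60 is 99.97%. What 60 per arm delivers depends on an SD the article does not pin down. If 2.5 is the SD of the analysed outcome, it is 90% power for about 1.5 (0.6 SD). If the SD is about 4.2, it is 90% for 2.5, and a control-arm improvement of a quarter of that brings power to about 68%.

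These figures assume a two-sided 5% two-sample t-test on a single waist outcome. The mixed model may behave somewhat differently. Whether power is in fact inadequate cannot be judged from the article. The correction should be made before results are interpreted, but the trial can run as designed.

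**What to change.** Keep both arms and the 160 participants.

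1. **Trial design, Control and Aim.** Describe the comparator as a delayed-access (waiting-list) control that receives general lifestyle education by e-mail and website. State the effectiveness hypothesis as the added change over that control, so that a null result is read as no demonstrated added benefit.
2. **Sample size.** Define the target as a between-arm difference in waist circumference, net of any control-arm change. State the SD of the analysed outcome and its source. Then restate what 60 completers per arm deliver: 90% power for a difference of about 1.5 (0.6 SD) if the SD is 2.5, or 90% for 2.5 if the SD is about 4.2. The sponsor should first establish from the original calculation which SD applies. Writing in 1.5 merely because it fits 60 would hide the discrepancy.

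The cost is rewording in four sections, with no new participants or procedures. The downside is a narrower claim and a restated detectable effect.

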### Primary outcomes

The primary outcomes are feasibility, acceptability, usability, and the change in metabolic syndrome components. Measures for assessing feasibility will include: the proportion of participants who respond to log-in to My Healthy Heart Profile for the first time, and response rate to postal follow-up for clinical assessments and complete the study questionnaires [77]. Acceptability will be explored by the number of sign-in to the My Healthy Heart Profile during intervention. Usability of the intervention will be accessed by the educational materials downloads and using of website components by participants. The change in metabolic syndrome components will be assessed by calculating changes in the following measures: waist circumferences, weight, blood pressure, triglycerides, HDL-cholesterol, and fasting blood glucose. Waist circumference will be measured in horizontal plane, midway between the lowest rib and the iliac crest with a measuring tape in centimeter [6]. The weight of individual dressed in light clothing without shoes will be measured at each time using a calibrated scale (Seca model 8811021658). Blood pressure will be measured with mercury sphygmomanometer twice in the same arm after the individual seated at rest 10–15 min. The systolic and diastolic measurement represents the mean of two readings. Blood sampling will be collected for measurements of total cholesterol, triglycerides, LDL-cholesterol, HDL-cholesterol, and fasting blood glucose for all participants. Overnight fasting for 12–14 h is needed before blood sampling. Venous blood samples (5 ml) will be collected. Body Mass Index (BMI) will be measured by individual’s weight divided by the square of the height [78].

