### Secondary outcomes

Secondary outcomes will include assessments of the followings:Health-related quality of life (HRQOL) using the SF-36 (Iranian version). The SF-36 is a very popular measure of health related quality of life among the general population. The psychometric properties of the Iranian version of the questionnaire are well documented [79],Physical activity using the International Physical Activity Questionnaire at last 7 days (IPAQ) [80], a well-validated questionnaire in Iran [81, 82];Food frequency using the validated Iranian version of Food Frequency Questionnaire (FFQ) [83], andPsychological well-being using the Iranian version of 12-item General Health Questionnaire (GHQ-12) [84].

Measurements will be made at baseline (T0), three (T1) and six (T2) months follow-up. Food frequency questionnaire will be completed only on T0 and T2.

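### Metabolic syndrome components: the plan tests changes with unadjusted t-tests and never says that the measured baseline enters any model, which costs some precision

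*Protocol article*

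**What the plan says.** The Primary outcomes section puts the clinical outcome on the change scale: "The change in metabolic syndrome components will be assessed by calculating changes in the following measures". The measures it then lists are waist, weight, blood pressure, triglycerides, HDL and fasting glucose.

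The Statistical analysis section names two methods. The first is "To test the study hypotheses t-tests for independent samples will be performed". The second, in the closing sentence, is "Between group differences will be evaluated by intent-to-treat analysis using the Generalized Linear Mixed Models (GLMM"). No covariate is named for either, and the section does not say which one supplies the primary result.

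Baseline values will be available. The schedule reads "Measurements will be made at baseline (T0), three (T1) and six (T2) months follow-up". The Trial design section gives the same three assessment points, and the Attrition prevention section has blood tests at all three. Baseline also precedes allocation: "Randomization will be carried out after baseline measurements".

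The other primary outcomes are usage and response measures, for example "Acceptability will be explored by the number of sign-in to the My Healthy Heart Profile during intervention". They have no pre-randomisation value.

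**The concern.** Each component has a pre-randomisation measurement that should predict its follow-up value. Subtracting it, as a change score does, in effect fixes the regression slope of follow-up on baseline at 1. When the true slope is below 1, this over-corrects in two ways. The comparison carries avoidable noise, and the arm that happens to start higher appears to improve more. Entry limits on waist and blood pressure make some regression to the mean likely for those two measures.

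At stake is the width of the interval for each component, and how far one trial's result depends on the baseline imbalance it happens to draw. The Sample size section is built on waist alone. Blood pressure, triglycerides, HDL and glucose are also primary and have no calculation of their own. If they track less closely over time than waist, which is plausible but not stated, the gain from adjustment is larger for them.

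**Working it through.** **1. The plan's own figure.** Inputs from the Sample size section: "The sample size was calculated based on one standard deviation decrease (2.5) [85] in waist circumference", 90% power, 5% level, 60 per arm raised to 80. The Statistical analysis section makes the level two-sided: "Two-sided p values of less than 0.05 will be regarded as statistical significant". A 1-SD difference needs

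n = 2 × (1.960 + 1.282)² / 1² = 21.0, so 22 per arm.

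The exact t calculation gives 89.97% power at 22 and 91.2% at 23. The stated 60 is therefore not reproduced; at 60 per arm, power for that effect is 99.98%. The step to 80 does follow from a 25% loss: 60/0.75 = 80. The mismatch is a separate matter. Here it shows only that, on the plan's inputs, waist has power to spare.

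**2. Precision.** Let σ be the SD at both baseline and follow-up (assumed equal), r their correlation (assumed; the documents give none) and n the number per arm.

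- Difference in mean changes: variance = (2σ²/n) × 2(1-r)
- Baseline-adjusted difference: variance = (2σ²/n) × (1-r²)
- Ratio = (1-r)(1+r) / [2(1-r)] = (1+r)/2

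| r | 2(1-r) | 1-r² | Ratio | SE reduction | 60 per arm becomes |
|---|---|---|---|---|---|
| 0.5 | 1.00 | 0.75 | 0.75 | 13.4% | 45 |
| 0.7 | 0.60 | 0.51 | 0.85 | 7.8% | 51 |
| 0.8 | 0.40 | 0.36 | 0.90 | 5.1% | 54 |
| 0.9 | 0.20 | 0.19 | 0.95 | 2.5% | 57 |

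The last column is the adjusted sample size with the same precision as 60 per arm analysed by change scores.

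**3. Restricted baseline.** Entry limits may narrow the baseline spread of waist and blood pressure. Suppose baseline variance is cut to a fraction k, with the slope still r and residual variance still 1-r². The change-score variance is then (1-r)²k + (1-r²), and the ratio becomes (1+r) / [(1+r) + k(1-r)]. With k = 0.5 (assumed):

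- r = 0.5: 1.5/1.75 = 0.86
- r = 0.7: 1.7/1.85 = 0.92
- r = 0.9: 1.9/1.95 = 0.97

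**4. Conditional shift.** Given a baseline difference of D SDs between arms, the change-score estimate moves by -(1-r)D. The chance imbalance at 60 per arm has SD √(2/60) = 0.18. A typical shift is therefore 0.5 × 0.18 = 0.09 SD at r = 0.5, 0.3 × 0.18 = 0.05 SD at r = 0.7 and 0.1 × 0.18 = 0.02 SD at r = 0.9.

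**5. Whether the mixed model already deals with this.** Suppose baseline enters as an ordinary repeated outcome, with a free mean for each arm at each visit and complete data. The arm-by-time contrast at 6 months is then

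(mean at 6 months - mean at baseline, intervention) - (mean at 6 months - mean at baseline, control),

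which is the difference in mean changes again. Precision is recovered only if baseline is a covariate or the arms are constrained to share one baseline mean. The text specifies neither.

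**The case against.** The strongest reply is that the mixed model is the planned between-arm analysis and may well adjust for baseline; a condensed article need not spell that out. This stands in part. A reader might infer that the plan never uses baseline, and the document does not support that, because it leaves the model's content open. But it does state the outcome scale and a covariate-free test of the hypotheses, and it does not rank the mixed model above that test.

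Second, the link between change scores and the t-test is made by reading two sections together. It is the natural reading, since change is the defined outcome, but no sentence states it. A t-test on final values, against which adjustment could look much better, is not stated either and is not used as the comparator here.

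Third, a reader might infer bias from the entry limits. Regression to the mean acts on both randomised arms alike, so the comparison of changes is unbiased on average. What remains is the conditional shift in step 4, which is small at typical imbalances. The entry limits concern only waist and blood pressure.

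Fourth, a reader might infer lost power, for instance by assuming a waist SD well above the 2.5 that the protocol gives. No larger SD appears in the document, and on its own inputs power at 60 per arm is 99.98%.

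What survives is a point about efficiency and clarity. A change-score analysis is conventional and not an error.

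**Conclusion.** The point holds for the metabolic syndrome components only. As written, the hypothesis test ignores baseline except by subtraction, and the planned mixed model is not specified in a way that improves on this. Adjustment would cut the variance by 25% at r = 0.5, 15% at 0.7, and 5 to 10% at r between 0.8 and 0.9, the range one might assume for strongly tracking measures such as waist or weight. These figures rest on an assumed r and on equal SDs; they shrink if entry limits compress the baseline spread. In large samples adjustment is never less precise than the change score. It also removes the dependence on chance imbalance described above. Neither average bias nor a power shortfall is shown. The change is worth making because it costs nothing in data and also settles which of the two named analyses governs.

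**What to change.** In the Statistical analysis section, name the intention-to-treat mixed model as the primary analysis of each metabolic syndrome component, in place of the t-test. Use the 3- and 6-month values as outcomes and that component's own baseline as covariate, and take the between-arm difference with its 95% confidence interval from this model. Report change scores by arm descriptively. State that the feasibility, acceptability and usability outcomes are outside this model because they have no baseline. The cost is one or two sentences; no new data, visits or participants are needed.
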